## **5.4 Subject Withdrawal from the Trial**

### **5.4.1 Reasons for Withdrawal (Premature Termination)**

After enrollment, a subject might be withdrawn from participation for several reasons:

- The investigator requests withdrawal of participation of the subject because the subject is not eligible or is no longer eligible, because the subject has developed an AE requiring withdrawal, or because the subject is non-compliant;
- A subject voluntarily withdraws participation at his/her own request;
- A subject is lost to follow-up; or
- The trial is terminated prematurely by the Sponsor or PVS.

### **5.4.2 Withdrawals at Specific Time-Points**

#### **5.4.2.1 Withdrawal of a Subject during Screening**

If after signing by the volunteer of the informed consent form (ICF) for screening (ICF A), the investigator ascertains during the screening period (from S1 to S2/Day 0) that the subject does not meet the inclusion/exclusion criteria, the subject should be assigned a study participant number but the CRF pages need not be completed. Only the reason for subject exclusion should be noted on an enrollment log.

#### **5.4.2.2 Withdrawal of a Subject as a Result of Erroneous Inclusion**

If a subject who does not meet the inclusion/exclusion criteria is inadvertently included in the trial, the investigator must terminate the subject's participation in the trial and the Sponsor and PVS should be informed. If the subject was randomized and was administered study vaccine or placebo, the subject should be maintained in the isolation unit for the specified period, if possible. However, the subject's data will be excluded from the analysis.

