## 4 Study Design

This is a phase I, double-blind, individually-randomized (3:1, vaccine:placebo), controlled trial with two groups, LAIV H7N3 and matched placebo. Healthy male and female adults 18 through 49 years of age will be invited to participate. For feasibility reasons and in order for an independent Safety Monitoring Committee (SMC) to review safety data in a small group of subjects initially, the total cohort of 40 subjects will be enrolled in two sub-cohorts: one cohort of 12 subjects, randomized at 3:1 (9 vaccine and 3 placebo), followed two weeks later by a second cohort of 28 subjects randomized at 3:1 (21 vaccine and 7 placebo). After all 12 volunteers of the first sub-cohort have been observed for the first isolation period (Day 1 to Day 7), an interim safety review will be performed by the SMC. The SMC will review all AEs, including clinical laboratory evaluations (pre- and post-vaccination) and shedding data, for all subjects and will advise if the volunteers of the first sub-cohort may receive dose two of study vaccine or placebo and if the additional 28 volunteers of the second sub-cohort may be enrolled into the study. As for the first sub-cohort, the SMC will also review all safety data for the second sub-cohort and for the entire participant population of the trial. For each sub-cohort, the procedures and timelines are here summarized.

On the day of first screening, about 7 days (between 4 and 14 days) prior to administration of dose one of study vaccine or placebo, subjects will be screened for eligibility through medical history review, physical examination, testing for serologic evidence of chronic viral infection [human immunodeficiency virus (HIV), hepatitis B virus (HBV) or hepatitis C virus (HCV), with proper pre- and post-test counseling], routine biochemical and hematological blood tests and urinalysis by dipstick.

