### 5.3.2 Masking Procedures

Study vaccine and placebo will have similar formulations (LAIV H7N3 is a lyophilized formulation which must be reconstituted with sterile water for injections and placebo is the same lyophilized material without vaccine virus). However, because study vaccine and placebo will be clearly labeled as such, an unblinded study clinician will be assigned to prepare all study vaccine and placebo preparations. This study clinician will not administer the preparations and will not reveal to either other study staff or to the subject which preparation was given. Preparation of study vaccine or placebo and filling of spray dosing devices will be done by the unblinded clinician behind a screen. Filled devices will be carefully handed to the blinded study clinician administering the preparation. Preparation of study vaccine and placebo and filling of spray dosing devices will be closely monitored by an independent monitor from PATH Vaccine Solutions (PVS) and a Sponsor representative. Adherence to randomization will also be closely monitored to confirm that the randomization scheme is not broken. Study vaccine or placebo given to each individual subject will be documented on the CRF with the appropriate allocation code. Full details will be specified in a *Masking* SOP prior to trial initiation.

All blinded study staff will remain blinded throughout the trial. If any subject develops an SAE possibly related to receipt of study treatment, treatment allocation to the subject may be communicated to the investigator only if that information is deemed necessary to properly treat the subject for the SAE. In such cases, PVS must be consulted prior to any unblinding.

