### **7.2.1 Day of First Admission into the Isolation Unit (Day 0)**

1. For eligible subjects, a study clinician will review the procedures for the vaccination study and admittance into the isolation unit. A vaccine study ICF (ICF B) should be completed at this time and the subject admitted into the isolation unit. Upon admittance into the isolation unit, a subject may proceed to undergo procedures related to administration of study vaccine or placebo and evaluation of vaccine safety and immunogenicity.
2. At least two hours prior to administration of study vaccine or placebo, a nasal swab specimen should be collected, followed one hour later by collection of a nasal wick specimen. Specimen collection information must be documented on the CRF and in specimen collection logs. Nasal wick specimens will be sent to IEM for mucosal anti-influenza IgA testing.
3. Prior to administration of study vaccine or placebo, a serum specimen will be collected for anti-influenza serologic assays. A whole blood specimen for isolating PBMCs for assessing cellular immune responses will also be collected at this time. Blood specimens will also be collected for testing a CMP and a CBC with differential. Specimen collection information must be documented on the CRF and in specimen collection logs. CMP and CBC with differential test results from specimens collected on Day 0 need not be obtained and reviewed prior to administration of study vaccine or placebo; these results will only served to define baseline status for subjects.
4. The subject will be administered one dose of study vaccine or placebo. Administration of study vaccine or placebo must occur at least one hour after collection of any nasal swab or nasal wick specimens from the subject.
5. The subject will be observed for two hours after administration in case of any immediate reactions. If the subject experiences an immediate adverse reaction, he/she will be treated and the event will be recorded on the CRF.
6. The subject will be observed throughout the day and any AEs that occur will be recorded in the appropriate section(s) of the CRF.
7. At least 6 hours after administration of study vaccine or placebo, a nasal swab specimen will be collected. Specimen collection information must be documented on the CRF and in specimen collection logs.

---

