### **11.2 Definition of Analysis Sets**

All primary safety descriptions and summaries will be performed on an intention-to-treat basis. Supportive per-protocol analyses will also be conducted on all enrolled participants who are randomized, receive two doses of study vaccines and complete the Day 56 visit.

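### Section 5.4.2.2 removes dosed but ineligible subjects from the analysis, while section 11.2 makes the primary safety analysis intention-to-treat; both rules cannot be followed

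*Protocol*

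**What the plan says.** Protocol section 5.4.2.2 covers a subject who fails the inclusion or exclusion criteria but is included by mistake. Participation is ended. The section explicitly reaches subjects who already have study product on board: "If the subject was randomized and was administered study vaccine or placebo, the subject should be maintained in the isolation unit for the specified period", where possible. The next sentence reads: "However, the subject's data will be excluded from the analysis". Nothing limits this to a particular endpoint or analysis set.

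Section 11.2 states: "All primary safety descriptions and summaries will be performed on an intention-to-treat basis". It then adds a supportive per-protocol analysis on "all enrolled participants who are randomized, receive two doses of study vaccines and complete the Day 56 visit". Meeting the eligibility criteria is not part of that definition.

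Section 3.1.1 makes the safety profile of two doses the only primary objective. Sections 3.2.1 and 11.3.1 express it as proportions of subjects with events, and 11.3.1 attaches exact 95% confidence intervals. Section 11.1 says that all objectives are descriptive and that no sample size is calculated.

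**The concern.** The two sections give different answers to a basic question: who is counted in the primary safety table? Someone following 5.4.2.2 deletes the subject. Someone following 11.2 keeps the subject. The protocol promises a later data analysis plan, but that plan could not settle the matter without departing from one of these sentences.

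The conflict matters more than the loss of a subject at random would, because ineligibility may come to light as a result of what happens after dosing. If a reaction leads staff to ask again about past illness, and the answer shows that a criterion was missed at screening, 5.4.2.2 takes out of the analysis the same reaction that prompted the question. In a phase I trial with few vaccinees, one such removal can take the only event of its kind out of the primary proportions.

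**Working it through.** **1. Can the sections be reconciled?**

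- *As a per-protocol rule.* Section 11.2 defines that set by randomisation, two doses and the Day 56 visit. An ineligible subject discovered late, who had both doses and attended Day 56, meets all three conditions. So 5.4.2.2 is not a restatement of the per-protocol definition.
- *As an immunogenicity rule.* Section 5.4.2.2 does not say so. The only immunogenicity exclusion in the protocol is the baseline-titre provision in 11.3.2, which is a different condition.
- *As a stated exception to intention-to-treat.* Section 11.2 lists no exception and does not refer to 5.4.2.2.

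No other section reconciles them. Section 16 leans the other way, since it expects the study report to reflect all safety data.

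**2. Can removal depend on outcome?** Compare the exclusion criteria (5.2) with the solicited reactions (9.2.1.2):

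| Exclusion criterion | Solicited reaction |
|---|---|
| History of asthma, or of wheezing after live influenza vaccine | Difficulty breathing, cough |
| History of seizures | Convulsions/seizures |
| Frequent nose bleeds in the past year | Nose bleeds |
| Acute respiratory illness within two weeks of enrolment | Runny nose, nasal congestion, sore throat |

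A reaction in the right-hand column is a natural prompt to revisit the history on the left. Blinding of the assessing staff does not prevent this: if the vaccine causes more reactions, more vaccinees face the review.

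**3. Size.** The protocol has no sample-size or power figure to reproduce. The arm sizes come from section 4:

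- Vaccine: 9 + 21 = 30. Placebo: 3 + 7 = 10. Check: 40 × 3/4 = 30.

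For x events in n subjects, the exact (Clopper-Pearson) 95% limits are the 0.025 quantile of Beta(x, n − x + 1) and the 0.975 quantile of Beta(x + 1, n − x). With x = 0 the lower limit is 0 and the upper limit is 1 − 0.025^(1/n).

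Assumption: one subject is removed under 5.4.2.2.

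| Scenario | All dosed subjects kept | One subject removed |
|---|---|---|
| One vaccinee with the event; that subject removed | 1/30 = 3.3% (0.1% to 17.2%) | 0/29 = 0% (0% to 11.9%) |
| Two vaccinees with the event; one of them removed | 2/30 = 6.7% (0.8% to 22.1%) | 1/29 = 3.4% (0.1% to 17.8%) |
| One placebo subject with the event; that subject removed | 1/10 = 10.0% (0.3% to 44.5%) | 0/9 = 0% (0% to 33.6%) |
| One vaccinee with the event; a different subject removed | 1/30 = 3.3% (0.1% to 17.2%) | 1/29 = 3.4% (0.1% to 17.8%) |
| No events; any vaccinee removed | 0/30 = 0% (0% to 11.6%) | 0/29 = 0% (0% to 11.9%) |

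In the first row the event disappears and the upper limit falls by 17.2 − 11.9 = 5.3 points. The last two rows show that loss of numbers alone is trivial. The same holds for the chance of seeing at least one event at an assumed true rate of 5%: 1 − 0.95^30 = 78.5% against 1 − 0.95^29 = 77.4%. Any harm comes from which subject is removed.

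**The case against.** The strongest reply is that the rule is narrow and the event is not hidden. Much of this is right:

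- Section 5.4.2.2 reaches only a criterion that was already present and was missed by two-stage screening. Illness arising after dosing falls under 5.4.2.3, which allows withdrawal but says nothing about excluding data.
- SAEs within one month of vaccination must be reported whatever their cause (9.3.1). The Safety Monitoring Committee reviews all AEs (section 4) and all SAEs (9.6.2). CRFs of all subjects are attached to the study report (section 16). A reader might infer that a safety signal could vanish from the trial. The documents do not support that: it would vanish from the tabulated primary proportions, not from oversight.
- A reader might infer that the rule always biases event rates downward. It does so only if the removed subject had the event; otherwise the rate rises very slightly.

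Three further extensions are tempting and should not be made:

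- *Day 0 laboratory results returning after dosing as a trigger for exclusion.* Section 7.2.1 does say "CMP and CBC with differential test results from specimens collected on Day 0 need not be obtained and reviewed prior to administration" of study product, but it goes on to give these results a baseline role only, and section 4 says they are not used for screening.
- *Lost follow-up.* Section 5.4.3 already asks for best efforts to complete the Day 28 or Day 56 evaluations after withdrawal for any reason.
- *Events credited to the wrong arm because ampoules are openly labelled.* Section 5.3.2 has preparation watched by an independent monitor and a Sponsor representative, and adherence to randomisation is monitored too. Misallocation is a contingency, and handling it is ordinary analysis-plan detail.

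Nor does the protocol describe this as a first safety trial; it says phase I. None of these points reconciles 5.4.2.2 with 11.2.

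**Conclusion.** The contradiction stands. As written, 5.4.2.2 removes randomised and dosed subjects from an analysis that 11.2 says is intention-to-treat, and no set defined in the protocol absorbs the exclusion. Because exclusion criteria overlap with solicited reactions, removal can depend on the outcome being measured.

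The size is conditional. With one reacting vaccinee removed, 3.3% (0.1% to 17.2%) becomes 0% (0% to 11.9%); with a non-reacting subject removed, almost nothing changes. This rests on an assumed single case, since the protocol gives no expected number, and on re-questioning after a reaction as the route to discovery. The trial is descriptive, so no test or error rate is affected. What is affected is the count in the only primary analysis, which should not be open to choice once outcomes are known.

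**What to change.** - **Section 5.4.2.2:** limit the data exclusion to the per-protocol and/or immunogenicity analyses, and name which.
- **Section 11.2:** state that every randomised subject who received any dose stays in the primary safety analysis, regardless of ineligibility found later.
- **Section 11.2, per-protocol definition:** add that the subject met the eligibility criteria, so that the exclusion has a defined place.

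The data analysis plan should carry the same wording, agreed before the database is frozen and the statistician is unblinded. The cost is a short protocol amendment. No new data collection is needed, because AEs are recorded for all subjects and 5.4.3 already seeks the post-withdrawal evaluations.

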#### **5.4.2.3 Withdrawal of a Subject as a Result of Appearance of Exclusion Criteria After Administration of Study Vaccine or Placebo**

If a subject develops a concomitant illness that is an exclusion criterion or, for any reason, requires treatment with unauthorized products, the subject may be withdrawn from the study. See Handling of Withdrawals and Concomitant and Unauthorized Products. In all such cases, the Sponsor and PVS should be consulted immediately.

#### **5.4.2.4 Withdrawal of a Subject for Violation of the Protocol**

A subject will be considered as largely not in compliance with the requirements of the protocol if any of the following conditions apply:

- Violation of the rules of the isolation unit;
- Substantially incorrect or incomplete completion of the self-observation diary;

- 
- Skipping a schedule visit;
  - Non-compliance at a scheduled visit (except cases of exclusion of volunteers from the trial) of any planned procedures; or
  - Failure to inform the investigator of the appearance of any AE or SAE in the subject.

#### **5.4.2.5 Withdrawal of a Subject as a Result of Withdrawal of Informed Consent**

If a subject wishes to withdraw consent for participation in the trial after the subject has been admitted to the isolation unit and has been administered dose one or dose two of study vaccine or placebo, the subject will be requested to complete evaluations for that day and to complete either Day 28 or Day 56 evaluations, as applicable. Besides, to ensure safety any subject exhibiting influenza virus shedding in a nasal swab specimen will remain in the isolation unit for a more prolonged period until results confirming that no influenza virus is detected in a nasal swab for at least two consecutive days are obtained.

If possible, the subject should indicate the reasons for the termination of participation. The subject will be informed that the public health authorities will be notified of the subject's premature discharge from the isolation unit, as well as of the results of rRT-PCR testing of the subject's nasal swab specimens for detection of viral shedding. The subject will be advised to remain at home and avoid close contact with other persons until 7 days post-administration of study vaccine or placebo have passed.

If a subject wishes to withdrawal consent for participation in the trial after the subject has been discharged from the isolation unit, the subject will be requested to return the self-observation diary card and complete either Day 28 or Day 56 evaluations, as applicable. If possible, the subject should indicate the reasons for the termination of participation.

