Subject screening for eligibility will continue and be completed on the second screening day (S2). This second screening day will occur the same day as scheduled admission to the isolation unit and administration of study vaccine or placebo (Day 0). Women will undergo pregnancy tests using urine samples. All subjects will undergo an ear, nose and throat (ENT) examination. Fully eligible subjects will be admitted to the isolation unit. At that time, nasal swab, nasal wick, and blood specimens will be collected for virologic and immunological testing prior to administration of study vaccine or placebo. Blood and urine specimens will be again collected for routine biochemical and hematological blood tests and urinalysis by dipstick; these results will serve to define baseline status for subject prior to receipt of study vaccine or placebo but will not be used for screening purposes. Subjects and investigators conducting assessments of safety will be unaware of which allocation, LAIV H7N3 or matched placebo, is received; study vaccine and placebo will be masked. Subjects will be carefully monitored for adverse reactions while in the isolation unit.

All subjects will remain in the isolation unit for at least 7 days after receipt of study vaccine or placebo. Nasal swabs will be collected daily while subjects are in isolation to test for

**Description of Study  
Design, cont.:**

presence of influenza virus shed in the nasal passage. Any subject exhibiting conjunctivitis will also have a conjunctival swab collected on the day of appearance of the sign. Any subject exhibiting influenza A virus shedding, as determined by real-time RT-PCR positivity on a nasal swab specimen, in the 2 days prior to each planned discharge day after each dose (Days 6 or 7 or Days 34 or 35) will be kept in the isolation until PCR-diagnosis results confirm that no influenza virus is present in a tested clinical specimen for at least two consecutive days.

Any subject still exhibiting evidence of influenza virus shedding in a nasal swab on Days 6 or 7 or Days 34 or 35 post-administration with each dose might be placed on influenza antiviral (oseltamivir) treatment at the standard dose for treatment of 75 milligrams (mg) twice a day for a course of 5 days.

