It is theoretically possible that vaccine virus that is replicating in a subject's upper respiratory tract may be shed and transmitted to those around the subject. If a subject decides to leave the isolation unit prematurely, the subject will be counseled on the theoretical risks to their household contacts and the community. The subject will also be told that local public health authorities might be notified of the subject's premature exiting from the isolation unit and that such authorities might quarantine the subject. A subject who is shedding virus is also potentially infectious to placebo recipients in the isolation facility. All subjects will be monitored closely for infection. (Study staff will be closely monitored outside of the study protocol and use of antivirals prophylactically during the dosing stages may be part of their terms of employment.)

Besides administration of study vaccine or placebo, collection of biological specimens (nasal swab, nasal wick, and blood specimens) may cause some discomfort to subjects. Collection of nasal swab and nasal wick specimens may cause mild discomfort or a tickling sensation in the nasal passages during the collection procedures. Venipuncture is sometimes associated with discomfort or pain, redness, swelling, and/or local hardness at the puncture site.

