### **5.4.3 Handling of Withdrawals**

In case of premature withdrawal for any reason, the investigator should exert his/her best effort to:

- 
- Conduct an interview to determine if the subject has had any reaction or AE (serious or non-serious) during the period one month after any study vaccination that has led to the withdrawal. Where possible, the investigator should visibly or physically assess any reported adverse reaction or AE.
  - Attempt to complete all scheduled procedures and evaluations planned for a) Day 28 (exclusive of administration of study vaccine or placebo) if premature withdrawal occurs prior to Day 28 but after administration of dose one of study vaccine or placebo or b) Day 56 if premature withdrawal occurs prior to Day 56 but after administration of dose two of study vaccine or placebo.
  - Document the reason for premature withdrawal on the CRF.

The trial Sponsor and PVS must be informed within 24 hours about all instances of the premature termination of a volunteer's participation in the trial. Any withdrawal that occurs while a subject is scheduled to be in the isolation unit requires immediate notification to the Sponsor and PVS. While participation in the trial is voluntary and subjects are free to withdraw consent at any time, subjects will be told that local public health authorities might be notified of any subject's premature exiting from the isolation unit. An SOP for the isolation unit will detail procedures to be followed for any withdrawal that occurs while a subject is scheduled to be in the isolation unit.

Withdrawal of a subject *by the investigator* may occur only if the subject is identified to have one of the listed exclusion criteria or if continued participation of the subject threatens the subject's well-being or the integrity of the study (or the well-being of other subjects in the isolation unit). After administration of dose one (or dose two) of study vaccine, a subject who is scheduled to be in the isolation unit may be withdrawn *by the investigator* only if the subject develops a reaction to study vaccine which the investigator believes threatens the subject's well-being; the withdrawn subject must be treated or transferred to a treatment facility.

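### Section 5.4.2.5 both retains a consent-withdrawing shedder in the isolation unit and provides for that subject's departure; for one who leaves, the home-stay advice ends at 7 days post-dose regardless of swab results

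*Protocol*

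**What the plan says.** For subjects in the unit, the Protocol Summary (Description of Study Design) and section 4 set a stay of at least 7 days after each dose. A subject who is PCR-positive on Day 6 or 7, or on Day 34 or 35, is kept until results "confirm that no influenza virus is present in a tested clinical specimen for at least two consecutive days". Section 7.2.8 makes ordinary discharge depend on negative swabs on both Day 6 and Day 7, and 7.2.17 does the same for Days 34 and 35.

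For a subject who withdraws consent after dosing while in the unit, 5.4.2.5 says three things:

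- Retention: "any subject exhibiting influenza virus shedding in a nasal swab specimen will remain in the isolation unit for a more prolonged period", until results confirm that "no influenza virus is detected in a nasal swab for at least two consecutive days".
- Departure: in the next paragraph, the subject is informed that the authorities will be "notified of the subject's premature discharge from the isolation unit, as well as of the results of rRT-PCR testing" of that subject's swabs.
- Advice: the subject is "advised to remain at home and avoid close contact with other persons until 7 days post-administration of study vaccine or placebo have passed".

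Other sections treat leaving as open to the subject. Section 2.3.1.1 says: "If a subject decides to leave the isolation unit prematurely, the subject will be counseled on the theoretical risks". It adds that authorities might be notified and might impose quarantine. Section 5.3.2 allows a subject's PCR positivity to be disclosed only when someone leaves the unit early. Section 5.4.3 says consent can be withdrawn at any time and that "subjects will be told that local public health authorities might be notified of any subject's premature exiting from the isolation unit".

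**The concern.** Section 2.3.1.1 names transmission of shed vaccine virus to people around the subject as a theoretical risk, and isolation is the main measure against it. A shedder who withdraws consent puts that measure to the test, and the text does not settle what happens then. Staff are told to keep the subject. The same section, with three others, is also written for the case in which the subject goes.

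If the subject does go, the only dated instruction given to the subject runs to a fixed day and ignores the swab results that justified isolation. The subject is also given two different statements about whether the authorities will hear of it. At stake are the safety of contacts and the accuracy of what subjects are told before and when they withdraw.

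**Working it through.** The protocol states no figure on this point to reproduce. The check compares the clauses and then counts days.

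**1. Retention against departure.** The retention sentence in 5.4.2.5 is mandatory and covers any shedding in a nasal swab. The departure paragraph that follows is not limited to non-shedders, and it provides for passing on shedding results. Section 5.3.2 expects that some early leavers will be PCR-positive. Sections 2.3.1.1 and 5.4.3 describe leaving and withdrawing as the subject's decision. No sentence says which clause prevails for a shedder who refuses to stay.

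**2. End of the home-stay advice against the in-unit standard.** Inputs: advice ends 7 days post-dose (5.4.2.5); clearance needs two consecutive negative days (Summary, section 4, 5.4.2.5); the day of dosing is Day 0 or Day 28. Let L be the day of the last positive swab, counted from the dose.

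Earliest in-unit clearance = L + 2. Shortfall of the advice = max(0, L + 2 − 7).

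| Last positive (dose one / dose two) | Earliest two-negative clearance | Advice ends | Shortfall |
|---|---|---|---|
| Day 5 / Day 33 | Day 7 / Day 35 | Day 7 / Day 35 | 0 days |
| Day 6 / Day 34 | Day 8 / Day 36 | Day 7 / Day 35 | 1 day |
| Day 7 / Day 35 | Day 9 / Day 37 | Day 7 / Day 35 | 2 days |

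The shortfall grows by one day for each further day of positivity. With a last positive before Day 5, the advice runs past the two-negative point.

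**3. Days of advice actually given.** For a subject leaving on post-dose day d, days of advice = max(0, 7 − d). Leaving on Day 6 gives 7 − 6 = 1 day. Leaving on Day 8 or later (Day 36 or later after dose two) gives 0 days. Subjects still in the unit then are those held over for late shedding. Section 8.2.2.1 limits later PCR swabs to subjects who remain admitted, so no swab is planned after departure.

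**4. Notification.** Section 5.4.2.5 informs the subject that "public health authorities will be notified of the subject's premature discharge from the isolation unit". Sections 2.3.1.1 and 5.4.3 have the subject told only that this might happen.

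**5. How many subjects.** The protocol gives no rate of late shedding or of early departure. Assume that 5% to 20% of the 30 vaccinees (9 + 21) shed late and that 5% to 10% of those leave:

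- low: 30 × 0.05 × 0.05 = 0.075
- high: 30 × 0.20 × 0.10 = 0.6

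**The case against.** The best defence reads 5.4.2.5 in sequence: shedders stay until clear, and the next paragraph tells non-shedders who leave early to complete the planned 7 days at home. On that reading the 7-day limit matches the planned isolation period and nothing conflicts. The reading is possible, but the text does not say it. The departure paragraph has no such restriction, and 5.3.2 expects PCR-positive leavers.

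Several objections do stand, and they rule out stronger conclusions that a reader might draw:

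- **That the community safeguard lapses.** It does not simply lapse. A leaver is counselled, the authorities receive the PCR results under 5.4.2.5, quarantine is possible under 2.3.1.1, and 5.4.3 requires immediate notice to the sponsor and its partner organisation for any withdrawal during a scheduled stay.
- **That the home-stay advice breaches the protocol's clearance standard.** The two-negative rule is written for stay in the unit. The advice departs from it but contradicts no written home rule, and it is shorter only from a last positive on Day 6 (Day 34 after dose two).
- **That the zero-day case follows from the rules as written.** It arises only if the retention clause is not carried out. What it shows is a missing fallback for a shedder who leaves anyway.
- **That freedom to withdraw consent is itself freedom to leave isolation.** These are not identical. The tension rests mainly on 2.3.1.1, 5.3.2 and the departure paragraph.

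Section 5.4.3 leaves in-unit withdrawal procedures to an SOP that is not shown. The SOP can add detail, but it cannot properly choose between two protocol clauses that point in different directions.

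**Conclusion.** The point holds as an unreconciled set of instructions. For a shedder who withdraws consent in the unit, the protocol does not settle whether the subject is kept or may go. If the subject goes, the advice has a fixed 7-day end-point with no swab condition: 1 day short of the in-unit standard for a last positive on Day 6, 2 days for Day 7, and 0 days of advice for anyone leaving during an extended stay. The statement on notification differs between sections.

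The practical size is small. Under the assumed rates about 0.08 to 0.6 subjects would be affected; those rates are assumptions, not protocol figures. No endpoint, analysis set or estimate changes. The point is worth correcting because it bears on the safety of contacts and on what subjects are told. The documents do not show which isolation, home-stay or notification rule is right, and no view is taken on that.

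**What to change.** Reconcile the following across the Protocol Summary, 2.3.1.1, section 4, 5.4.2.5 and 5.4.3, and carry the result into the isolation-unit SOP and the subject information:

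- the retention clause and the subject's right to leave, stating what applies to a shedder who will not stay;
- the end-point of the home-stay advice for a subject with a recent positive swab, and how it relates to the two-negative-day standard used in the unit;
- whether the departure paragraph of 5.4.2.5 covers shedders, non-shedders or both;
- one statement on whether authorities *will* or *might* be notified, identical wherever subjects are told about it.

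The sponsor and the ethics committees decide which rule applies. The cost is wording in the protocol, the SOP and the subject information. The reconciliation itself needs no extra visits, specimens or subjects.
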